## Abstract

Keloid scars are characterized by the excessive proliferation of fibroblasts and an imbalance between the production and degradation of collagen, leading to its buildup in the dermis. There is no “gold standard” treatment for this condition, and the recurrence is frequent after surgical procedures removal. *In vitro* studies have demonstrated that photobiomodulation (PBM) using the blue wavelength reduces the proliferation speed and the number of fibroblasts as well as the expression of TGF-β. There are no protocols studied and established for the treatment of keloids with blue LED. Therefore, the purpose of this study is to determine the effects of the combination of PBM with blue light and the intralesional administration of the corticoid triamcinolone hexacetonide on the quality of the remaining scar by Vancouver Scar Scale in the postoperative period of keloid surgery. A randomized, controlled, double-blind, clinical trial will be conducted involving two groups: 1) Sham (n = 29): intralesional administration of corticoid (IAC) and sham PBM in the preoperative and postoperative periods of keloid removal surgery; and 2) active PBM combined with IAC (n = 29) in the preoperative and postoperative periods of keloid removal surgery. Transcutaneous PBM will be performed on the keloid region in the preoperative period and on the remaining scar in the postoperative period using blue LED (470 nm, 400 mW, 4J per point on 10 linear points). The patients will answer two questionnaires: one for the assessment of quality of life (Qualifibro-UNIFESP) and one for the assessment of satisfaction with the scar (PSAQ). The team of five plastic surgeons will answer the Vancouver Scar Scale (VSS). All questionnaires will be administered one, three, six, and twelve months postoperatively. The keloids will be molded in silicone prior to the onset of treatment and prior to excision to assess pre-treatment and post-treatment size. The same will be performed for the remaining scar at one, three, six, and twelve months postoperatively. The removed keloid will be submitted to histopathological analysis for the determination of the quantity of fibroblasts, the organization and distribution of collagen (picrosirius staining), and the genic expression of TGF-β (qPCR). All data will be submitted to statistical analysis.

**Trial registration:** This study is registered in ClinicalTrials.gov (ID: NCT04824612).

## Introduction

A keloid is a raised scar characterized by the excessive proliferation of fibroblasts and an imbalance between the production and degradation of collagen, leading to its buildup in the dermis. Keloids do not regress spontaneously and surpass the line of the scar with disorganized, uneven growth [1–5]. Besides the unpleasant esthetic aspect, keloids are often painful and pruritic and can lead to functional disability when occurring on joints. This combination of factors exerts a negative impact on psychosocial aspects and quality of life [6, 7]. Keloids do not regress spontaneously and surpass the line of the scar with disorganized, uneven growth [1–5]. Besides the unpleasant esthetic aspect, keloids are often painful and pruritic and can lead to functional disability when occurring on joints. This combination of factors exerts a negative impact on psychosocial aspects and quality of life [6, 7].

The genesis of this condition is not yet fully understood due mainly to the lack of *in vivo* studies and the fact that keloids are not described in animals, which hinders the adequate biological study of this entity [1, 2, 7, 8]. However, studies have demonstrated that the inflammatory aspects [9] and hyperproliferation of fibroblasts is related to an increase in the expression of transforming growth factors beta 1 (TGF-β1) in endothelial cells during the process of neovascularization, which already have a high expression of vascular endothelial growth factor (VEGF) as well as an increase in the expression of connective tissue growth factor (CTGF) [4, 7, 10–14].

TGF-β plays a key role in the regulating the proliferation of fibroblasts and the synthesis of collagen. In the normal healing process, TGF-β levels diminish at the end of the tissue repair process. However, this does not occur in the case of keloids, where TGF-β remains high and dysregulated [2, 15, 16].

The literature reports several treatments for keloids, but many studies employ questionable methods and report imprecise results, which hinders the establishment of new treatment protocols. Thus, there is no consensus on the best therapy to minimize the risk of recurrence with minimal undesirable side effects [7, 10, 11, 17–29].

The intralesional administration of the corticoid triamcinolone hexacetonide (Triancil®, Apsen Farmacêutica S.A.) is considered the first line of treatment for keloids, with an established dose of 2.5 to 20 mg for facial skin and 20 to 40 mg for other regions of the body. Its mechanism is based on the reduction in the synthesis of collagen and glycosaminoglycans as well as the inhibition of fibroblast production [30]. Due to its anti-inflammatory and vasoconstrictive effects, reductions in pruritus and pain also occur. Studies report a variable recurrence rate of up to 50% [7, 18, 31–33].

There is no consensus on the quantity or time of treatment for the triamcinolone hexacetonide corticoid. Prolonged use can lead to ulcers, changes in the color of the skin, and the emergence of telangiectasias [7]. There are also reports of the reappearance of Cushing syndrome after its use [18, 30–33]. Besides these side effects, the isolated use of the corticoid often does not lead to the complete regression of the keloid and can result in unappealing residual scars, with a color change, broadening of the scar, telangiectasias, and depressions [18, 33].

Combined therapy involving surgical excision and the use of the injectable corticoid has demonstrated to be safety, with a little reduction in the recurrence rate by about 29% [34–39]. However, the considerable variation in the protocols and results hinders a precise evaluation.

Due to the high recurrence rate with the use of current treatments, a keloid can remain for a long time, causing a reduction in one’s quality of life [6]. This situation has led to the search for novel, minimally invasive products and technologies that can offer better treatment with fewer side effects and a lower recurrence rate.

Considering this context and these characteristics, the benefits of photobiomodulation (PBM) have been listed in the literature. The PBM consists of the use of low-intensity light sources (normally less than 500 mW) with non-ionizing irradiation in both the visible band (400–760 nm) and infrared band (760–1000 nm) of the electromagnetic spectrum, producing a positive biological effect on cells [40, 41].

Studies have reported the benefits of PBM on the healing process of postoperative scars from different types of surgery, demonstrating the safety and effectiveness of this form of therapy [42–51]. *In vitro* experimental studies using fibroblasts from keloids and human dermis have also demonstrated positive effects, such as an increase in the apoptosis rate and reduction in the cell division rate of these fibroblasts as well as reductions in the synthesis of collagen and the expression of TFG-β [10, 52–59].

Blue light (wavelength ranging from 410 to 480 nm), in particular, is reported to have in inhibitory effect on fibroblasts and TGF-β when administered with a higher energy density (up to 640 J/cm^2^) [10, 52–59].

It is possible that blue light interacts with mitochondrial chromophores in the same way as red and infrared light, as heme centers in cytochromes have significant peak absorption that coincides with the Soret band of porphyrins [60]. In the blue light spectrum, porphyrins and flavoproteins, such as NADH-dehydrogenase and succinate dehydrogenase, can function as photoreceptors [61].

An important aspect to emphasize is the low cost of the LED, as many studies show that in photobiomodulation it has the same effect as lasers [62].

Studies reporting the beneficial effects of PBM on the healing process suggest a promising path for the establishment of this therapeutic modality in the treatment of keloids. Therefore, the purpose of this study is to determine through a randomized and controlled clinical trial the effects of the combination of PBM with blue light and the intralesional administration of the corticoid triamcinolone hexacetonide on the quality of the remaining scar by Vancouver Scar Scale in the postoperative period of keloid surgery. Also, the recurrence rate, its volume, the histopathological analysis, and thequality of life.

## Methods

### Study design

This study protocol was designed as a prospective, randomized, double-blind, controlled trial according to the 2013 SPIRIT (Standard Protocol Items: Recommendations for Interventional Trials) Statement (S7 File) and SPIRIT figure (Fig 1) and will be conducted at Nove de Julho University and Mandaqui Complex Hospital in Brazil in 2021–2023.

**Fig 1 pone.0263453.g001:**
[figure not shown]
SPIRIT figure as recommended by 2013 SPIRIT statement.

### Sample size and participants

The sample size was calculated considering a significance level of 0.05 and 80% power to obtain the means of improvement at three months postoperatively using the Vancouver Scar Scale (corticoid group: mean = 1.95; SD = 1.84) based on the paper by HEWEDY *et al*. [63]. Due to the lack of data in the literature regarding the study group, we estimated the same variability found in Group 1 (G1 1.95 vs. G2 0.25, difference of 1.7). Considering a 10% dropout rate, a total of 58 participants will be recruited: N = 29 per group. All participants will be recruited from the Mandaqui Hospital Complex and Nove de Julho University as well as through announcements in digital media.

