### Statistical analysis

The Kolmogorov-Smirnov test will be used to determine the normality of the data. Variables with parametric distribution will be submitted to one-way analysis of variance (ANOVA) followed by Tukey’s test for comparisons between groups. Variables with nonparametric distribution will be submitted to the Kruskal-Wallis test followed by Dunn’s post hoc text for comparisons between groups. The significance level will be set at α = 5%.

Original study forms will be entered and kept on file at the participating site. When a form is selected, the participating site staff will pull that form, copy it, and sent the copy to the data coordinating center. Participants’ files will be stored in numerical order and stored in a secure and accessible place and manner. They will be maintained in storage for a period of 05 years after completion of the study. The primary author will be responsible for the database on its own device and in the storage cloud. He has no conflicts of interest and no funding.

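### The sample-size inputs conflict with the trial's hypothesis as worded, and the stated 80% power does not lead to 29 per group

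*Protocol article*

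**What the plan says.** All the inputs are in the Protocol article, Sample size and participants.

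- Error rates: "The sample size was calculated considering a significance level of 0.05 and 80% power". Statistical analysis repeats the 5% level. Neither section says whether the test is one- or two-sided.
- Quantity powered: "means of improvement at three months postoperatively using the Vancouver Scar Scale".
- Comparator: "corticoid group: mean = 1.95; SD = 1.84", taken from a cited paper.
- Study arm: the article says that published data for this group are lacking, so "we estimated the same variability found in Group 1". The means are "G1 1.95 vs. G2 0.25, difference of 1.7".
- Size: 10% dropout is allowed for, giving 29 per group and 58 in total.

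The Abstract fixes the numbering, with "1) Sham (n = 29): intralesional administration of corticoid (IAC) and sham PBM" as group 1 and active photobiomodulation plus corticoid as group 2. The Discussion hypothesises that the active treatment improves the appearance of the scar and lowers the risk of recurrence. The article gives neither the range nor the scoring direction of the Vancouver Scar Scale.

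**The concern.** Two things in the same short paragraph do not fit together.

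First, the meaning of 1.95 and 0.25. If they are improvements, as the text says, the planned effect favours the sham arm. If they are scores at three months with lower values better, the direction is right. The study arm then sits almost at the floor of the scale, where the comparator's SD does not belong. Each reading has a defect, and a reader cannot tell which was meant.

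Second, the link between the stated power and the stated size. The paragraph gives everything needed to recompute N, and the result is not 29.

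What is at stake is how the result is read. The sample-size paragraph defines the difference the trial was built to detect. If the scale, direction and power of that difference are unclear, a null result at three months cannot be placed: the reader does not know which differences the trial was likely to find and which it was likely to miss.

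**Working it through.** **Inputs.** Difference 1.7, SD 1.84 in both arms, alpha 0.05, power 80%, dropout 10%, 1:1 allocation (all from Sample size and participants). Two-sided testing is my assumption.

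**1. The stated size.** The normal approximation is n per arm = 2 × SD² × (z₁₋α/₂ + z₁₋β)² / difference².

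- 80% power: 2 × 1.84² × (1.960 + 0.842)² / 1.7² = 18.4, so 19 per arm. The t-test needs 20.
- After dropout: 19/0.9 = 21.1, so 22; 20/0.9 = 22.2, so 23. The total is 44 to 46, not 58.

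Variants, per arm after dropout:

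| Variant | Per arm after dropout |
|---|---|
| Two-sided 80%, normal / t-test | 22 / 23 |
| One-sided 80%, normal / t-test | 17 / 18 |
| Two-sided 80%, rank test, relative efficiency 0.955 / 0.864 | 24 / 27 |
| Two-sided 90%, t-test | 26/0.9 = 28.9, so 29 |
| One-sided 95%, normal | 29 |

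No variant tried at 80% power reaches 29. A two-sided t-test at 90% power gives it exactly. Whether that is how 29 arose cannot be known from the article.

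**2. Direction.** If the figures are improvements, active minus comparator is 0.25 − 1.95 = −1.7, so the active arm improves less. The 1.95 is labelled as the corticoid group's mean, and the arm without published data is the study group, so the arms cannot be swapped to remove the conflict.

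**3. The SD under the score reading.** For a score between 0 and M with mean m, the largest possible SD is √(m(M − m)), reached only when every patient scores either 0 or M. With m = 0.25:

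| Assumed maximum M | Largest possible SD |
|---|---|
| 12 | 1.71 |
| 13 | 1.79 |
| 14 | 1.85 |
| 15 | 1.92 |
| 20 | 2.22 |

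SD 1.84 requires M ≥ 0.25 + 1.84²/0.25 = 13.79. Below that it is impossible. At 14 or 15 it needs about 2% of patients near the maximum and nearly all others at 0. Under this reading the assumed effect also removes 1.7/1.95 = 87% of the comparator mean.

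**4. What the fixed size delivers.** 29 × 0.9 = 26.1, so 26 evaluable per arm. Two-sided t-test, SD 1.84 in both arms:

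| True difference | Power, 26 per arm | Power, 20 per arm (the size that 80% for 1.7 implies) |
|---|---|---|
| 1.7 | 90% | 81% |
| 1.46 | 80% | 69% |
| 1.2 | 64% | 52% |
| 1.0 | 48% | 39% |

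**5. Effect of an SD that is too large.** With 26 per arm, a difference of 1.7 and a comparator SD of 1.84, a study-arm SD of 1.0 gives 98.5% power and 0.5 gives 99.5% (normal approximation), against 91% with equal SDs by the same method. Correcting the SD raises power.

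**The case against.** The strongest reply is that none of this harms the trial's power. A two-sided comparison of means uses only the size of the difference and the SD, so a reversed label changes neither N nor power. An SD that is too large is conservative. On the article's own inputs, 26 evaluable per arm exceeds the stated 80%. All of this stands.

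A reader might therefore be tempted by two stronger conclusions that the document does not support:

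- *That the power statement has no valid basis.* The difference and SD as given do support at least 80% power with 29 per group. The faults are in what the numbers are said to measure and in the power figure attached to them.
- *That the trial is underpowered compared with what its text implies.* The reverse is true. At every difference tabulated, 26 per arm has more power than the roughly 20 per arm that 80% power for 1.7 implies. Lower power for smaller effects holds for any trial, and nothing in the article shows that 1.0 point is the realistic benefit.

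Two further replies stand in part. The SD objection depends on a scale range that the article does not give, so strict impossibility holds only for a maximum below about 13.8. If the figures are changes from baseline, negative values are allowed and SD 1.84 is feasible, but the direction conflict then returns. It is also fair that a fuller reason for 1.7 may be in the trial files that the article mentions and that are not shown. The absence of a reason is therefore not held against the plan. What remains is what the article states: a label against the hypothesis, and a power figure that does not produce the stated N.

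**Conclusion.** The sample-size paragraph needs correction on two counts.

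1. As worded, its means contradict the hypothesis by 1.7 points. This needs no assumption beyond the article's own word, improvement. The score reading restores the direction but makes the equal-SD assumption implausible. That part assumes a floor of 0 and a scale maximum of about 15 or less, and the resulting error is on the safe side for power.
2. The stated 80% power and 29 per group do not belong together. With two-sided testing, 80% needs 23 per arm after dropout by t-test; 29 corresponds to 90%.

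Both are errors of statement. The planned size is adequate for the difference named, and there is no ground for changing N.

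**What to change.** Keep N = 58 and rewrite the sample-size paragraph:

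- State whether 1.95 and 0.25 are Vancouver Scar Scale scores at three months or changes from baseline, and give the scale's range and which direction is better.
- Justify 0.25 and the equal SD, or drop them and name only the difference and the SD used.
- State the sidedness of the test.
- Replace the power statement with: *26 evaluable participants per arm give 90% power for a 1.7-point difference and 80% power for 1.46 points at SD 1.84 (48% for 1.0 point), two-sided t-test at the 5% level.*

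The cost is a few sentences. Recruitment, procedures and analysis stay as they are, and the restated power for 1.7 points is higher than the figure now printed.

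### The printed sample-size inputs give 22 to 23 participants per group at 80% power, not 29; 29 per group matches 90% power

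*Protocol article*

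**What the plan says.** The section Sample size and participants of the protocol article prints a complete set of inputs:

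- Error rates: "a significance level of 0.05 and 80% power".
- Endpoint: Vancouver Scar Scale at three months after surgery, with control values taken from a published study ("corticoid group: mean = 1.95; SD = 1.84").
- Variability in the study arm, for which no data were available: "we estimated the same variability found in Group 1".
- Target: "G1 1.95 vs. G2 0.25, difference of 1.7".
- Result: "Considering a 10% dropout rate, a total of 58 participants will be recruited: N = 29 per group".

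The section gives no inflation other than dropout. The abstract and the section on randomization repeat 29 per group. The statistical analysis section sets the same level ("The significance level will be set at α = 5"%) and does not mention splitting it.

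**The concern.** With a difference of 1.7 and an SD of 1.84, the standardised effect is about 0.92. An effect that large needs roughly 20 evaluable participants per group at 80% power, so 29 is too many for a 10% dropout allowance to explain.

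The power statement is the figure against which a null result will be read, and 58 is the enrolment target. If 80% was the true aim, 12 to 14 more people undergo keloid excision than that aim requires, with no reason given. If a higher power was the aim, the article understates it, and readers will misjudge which differences the trial could have detected.

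**Working it through.** **Inputs** (all from the section Sample size and participants): difference Δ = 1.95 − 0.25 = 1.7; SD σ = 1.84 in both groups; α = 0.05; power 80%; dropout 10%; 1:1 allocation. Sidedness is not stated, so two-sided is assumed first.

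**Standardised effect:** d = 1.7/1.84 = 0.924.

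**Attempt to reproduce 29 at 80% power**

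Normal approximation: n = 2(z₀.₉₇₅ + z₀.₈₀)²/d² = 2(1.960 + 0.842)²/0.924² = 18.4, so 19 evaluable per group.

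Exact two-sample t-test (noncentral t, 2n − 2 degrees of freedom, noncentrality d√(n/2)): n = 19.4, so 20 evaluable per group. Power is 79.1% at 19 and 81.3% at 20.

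Adding 10% dropout to the t-test size:

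- 20/0.9 = 22.2, so 23 per group, 46 in total
- 20 × 1.1 = 22 per group, 44 in total

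The normal approximation gives 19/0.9 = 21.1, so 22 per group. The printed 29 is not reproduced. The gap is 6 to 7 per group, or 12 to 14 in total, and 58/46 = 1.26.

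**Same t-test at other power levels (two-sided 5%)**

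| Power | n exact | Evaluable per group | Recruited per group (÷ 0.9) | Total |
|---|---|---|---|---|
| 80% | 19.4 | 20 | 23 | 46 |
| 85% | 22.04 | 23 | 26 | 52 |
| 90% | 25.6 | 26 | 29 | 58 |

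The 90% row gives the printed size exactly (26/0.9 = 28.9).

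**What 29 per group delivers on the printed inputs**

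- 26 completers per group (29 less 10%): power 90.4% for 1.7 points
- all 29 per group: power 93.3%
- 26 completers per group: difference detectable at 80% power is 1.46 points

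**Could another route give 29 at 80% power?**

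- One-sided 5%: 16 evaluable, 18 recruited per group. The gap widens.
- Rank-test allowance with relative efficiency 0.955: 19.4/0.955 = 20.3, so 21 evaluable and 24 recruited.
- Rank-test allowance at the worst-case efficiency of 0.864: 19.4/0.864 = 22.5, so 23 evaluable and 26 recruited. Rounding to 20 first gives 20/0.864 = 23.1, so 24 and 27. The total is 52 to 54, still below 58.
- Larger dropout: 20 completers out of 29 means 1 − 20/29 = 31%, against the printed 10%.
- Larger SD: about 2.14 with 26 completers, against the printed 1.84.

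**The case against.** The strongest objection concerns the diagnosis. That the calculation was run at 90% power is an inference, and other routes also lead to 29. A one-sided 5% normal calculation at 95% power gives 26 evaluable and 29 recruited. A two-sided test at 0.05/3 has 79.99% power with 26 evaluable per group, so an undisclosed step could lie behind the number while 80% is correct. This is fair as far as it goes: the text does not show which step was taken. Neither route rescues the passage, though. The first contradicts the printed 80%, the second contradicts the printed 0.05, and strict rounding in the second gives 27 evaluable and 30 recruited.

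A second objection is that the analysis section allows rank-based tests for non-normal variables, and a worst-case allowance narrows the gap to 2 or 3 per group. The sample-size section mentions no such allowance, and the allowance still does not reach 58.

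A third is that an article may leave the test, sidedness and formula to a fuller document. That is accepted, and their absence is not the complaint. The point is that the printed inputs and the printed output disagree.

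Last, the error is conservative: 29 per group satisfies a requirement of at least 80%, and error control is unaffected. That stands and limits the seriousness of the point.

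**Conclusion.** The point holds. On the printed inputs, 80% power requires 22 to 23 recruited per group (44 to 46 in total) and not 29 (58). The planned total is 12 to 14 above that, or 26% more than 46. This rests on a two-sided 5% two-sample t-test with a common SD of 1.84. A one-sided test makes the discrepancy larger, and a rank-test allowance reduces it without removing it.

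The closest conventional explanation is a 90% power calculation, which gives 29 exactly, but the document does not confirm it. Whatever was intended, 29 per group with 10% dropout gives 90.4% power for 1.7 points on the article's own assumptions. The trial is therefore not underpowered for its target. The power statement is wrong as written and should be corrected.

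**What to change.** Keep 58 and correct the sentence in the section Sample size and participants. It should say that 26 evaluable participants per group give 90% power to detect a 1.7-point difference (SD 1.84, two-sided 5% t-test), or equivalently 80% power for 1.46 points, and that 29 per group are recruited to allow for 10% dropout. These statements hold on the printed inputs whatever calculation was first run.

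The sponsor should check the original calculation before making the change. If it contained a further step, such as a different significance level or an extra allowance, that step should be stated so that inputs and result agree.

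The cost is one sentence. Enrolment, randomization and the group sizes given elsewhere in the article do not change.
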